### Study population

#### *Inclusion criteria*

• Non-haemorrhagic or haemorrhagic cortical, subcortical, or subcortico-cortical stroke;

• Presence of aphasia for at least 6 months;

• Age between 18 years and 70 years;

• German as (the first) native language;

• A score of at least 1 (between 0 and 5) on the communicative ability scale of the Aachen Aphasia Test/AAT [27];

• Less than the maximum score of 10 error points on the first of five subtests of the AAT Token Test (securing basic comprehension of spoken instructions).

In cases in which potential participants have been appointed a guardian, the guardian’s written approval to participation in the trial is required in addition to the signature of the patient. Further, if the patient has a guardian, the attending physician is asked to attest a patient’s ability to decide for him- or herself whether or not he or she wishes to participate.

#### *Exclusion criteria*

• No verifiable aphasia according to the criteria of the AAT;

• Aphasia due to traumatic brain injury or neurodegenerative diseases;

• Severe uncontrolled medical problems;

• Severe uncorrected-to-normal visual or auditory impairment;

• Participation in an alternate intensive intervention to relieve stroke symptoms during the past four weeks prior to enrolment.

### Therapy

Therapy consists of a combination of language-systematic and communicative-pragmatic approaches. In order to tailor therapy to the individual needs of the patients, we designed specific screening measures by which the individual severity of impairment across the various domains of language and communication may be identified in each patient prior to therapy. These screening measures examine language-systematic as well as communicative-pragmatic language functions. Individual therapy targets are set upon identification of performance levels in the screening measures. Contents of therapy are determined by a detailed standardized therapy manual which allows (i) establishment of a therapy plan tailored to the individual patient’s focus and level of language impairment(s); and (ii) adaptation of therapy material and/or therapy methods to the expected improvements in linguistic and communicative ability over the course of therapy^b^. Participants’ progress is monitored daily, and monitoring results as well as therapy content are documented by the attending therapists. All therapists in the participating centres underwent comprehensive training with the therapy manual prior to patient recruitment.

### Study design

The study design is depicted in Figure 1. The inclusion of a waiting list control group, intended to control unspecific effects of language therapy, circumvents the ethical dilemma of withholding potentially efficacious treatment from patients. After a 3-week waiting period, the control group receives the same treatment as the experimental group.

**Figure 1 F1:**
[figure not shown]
Trial design.

A particular design aspect, namely the repeated test points t2b and t3b of Figure 1, is due to the heterogeneity of current therapy funding by German health funds. Initial funding is generally granted for 3 to 4 weeks, and may be extended for up to 7 weeks *during* the rehabilitation phase for some of the patients. For statistical reasons, we fixed a test point immediately after the 3-week intensive therapy (i.e., t2 and t3, respectively, in Figure 1) which includes *all* patients enrolled in the study. Whenever a patient’s individual funding period comprises at least 5 weeks of therapy, testing is repeated at the end of this patient’s total therapy period (i.e. t2b/t3b in Figure 1). The additional test point serves to measure further potential improvements beyond the initial 3-week therapy period. Initial screening, baseline testing, and follow-up tests are performed by specially trained 'study assessors’ (SAs), all with long-term experience in diagnosis and treatment of neurogenic speech and language disorders. All of the screening measures and tests are scored by the assessing SAs, and validated by an internal data review process, except for the primary outcome measure (see below). The primary outcome measure is evaluated by a specially trained endpoint committee (8 members) which is blinded with respect to patient group and time of assessment.

### Outcome measures

#### *Primary endpoint*

Mean difference on the ANELT [28] A-scale (understandability), operationalized as the difference in scores between the test point immediately after the 3-week intensive therapy (or waiting) period, and the test point immediately prior to the initiation of treatment (i.e., the difference of the scores, i.e., 't2’ minus those at test point 't1’; Figure 1). The ANELT tests verbal communicative ability in everyday communicative situations, shows a high concurrent validity with other standard linguistic assessment tools and is particularly suitable in the post-acute/chronic phase after stroke.

#### *Key secondary endpoint(s) (exploratory analysis)*

(i) Specially devised screening measures for language-systematic and communicative-pragmatic communication ability; (ii) the German version of the Stroke and Aphasia Quality of Life Scale-39/SAQOL-39 [29]; (iii) German Version of the Communicative Effectiveness Index/CETI [30]; (iv) B-scale (intelligibility) of the ANELT scenarios [28]; (v) ratings of the syntactic complexity of the ANELT scenarios using the AAT scoring system for spontaneous speech [27]; (vi) ratings of non-verbal communication skills on the ANELT scenarios (based on the Scenario test [31]).

To minimize practice effects due to repeated testing, the two parallel versions of the ANELT are alternated across testing sessions (retest reliability of the ANELT-I and ANELT-II: r >0.92 for the A-scale, r >0.74 for the B-scale [32]). Retest reliability of the other secondary outcome measures relating to quality of life is also satisfactory (CETI: r = 0.73, SAQOL-39: r = 0.98).

### Procedure

As part of the informed consent, patients are informed that the trial comprises an experimental condition and a waiting list (with a 3 week waiting period) condition. Patients who agree to participate are randomized to either the intensive therapy or the waiting list group, stratified according to centre, by a randomization procedure conducted in a central database by the Institute of Clinical Epidemiology and applied Biometry at the University of Tuebingen, Germany.

The outcome of the randomization procedure is communicated to the respective head of the SLT unit at each cooperating centre (Table 1) who is the only person to be informed about group allocation determined by the randomization procedure. Thus, the speech therapists conducting therapy are not informed about group allocation. Depending on their group assignment, patients either start therapy immediately (experimental group) or 3 weeks after the initial baseline session. The scoring of the primary endpoint (ratings on the ANELT A-scale) and the secondary ANELT endpoints is conducted independently from the therapists and study assessors performing the pre- and post-therapy assessments. That is, ANELT scoring is performed by an endpoint committee consisting of 8 raters, who are experienced in ANELT administration and scoring, and who have been specially trained to perform ANELT scoring in this trial. ANELT scorers are not involved in any other aspect of the trial in order to keep them blinded to group allocation (experimental, waiting list) and testing session (baseline or follow-up). Scoring of the ANELT is based on audio- and video-recordings collected by the study assessors. Each recording of an ANELT test is independently evaluated by two members of the endpoint committee; across the eight raters, the distribution of ANELT recordings for each patient follows a pseudo-randomized strategy.

### Power calculation

Sample size calculation was conducted for the comparison of mean change in ANELT A-scale score from t1 (baseline) to t2 (after 3 weeks of therapy or waiting) between the intensive language therapy group and the waiting list group (Figure 1). As a minimum difference of 8 points on the ANELT A-scale is considered clinically significant [32], group sample sizes of 63 were specified for each group in order to achieve 90% power to detect a difference of 10 points in the improvement of the mean ANELT A-scale score between the intensive treatment group after 3 weeks of intensive therapy and the waiting list group (difference of 1 point after 3 weeks of waiting), assuming a standard deviation for the difference in the ANELT A-scale score between t2 and t1 of 14 (10 for the waiting list group; Figure 1). Sample size was calculated for a two-sided Mann-Whitney test with significance level (alpha) of *P* <0.05. Assuming a patient non-participation rate of 25% prior to official study inclusion by randomization (for example due to the presence of exclusion criteria or no therapy funding by the respective sickness fund), 2 × 84 = 168 patients have to be recruited. The assumption of non-parametrical testing is rather conservative and the actual power will be larger if parametrical testing is possible.

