**Methods/Design:**

Participants are men and women aged 18 to 70 years, at least 6 months post an ischemic or haemorrhagic stroke resulting in persisting language impairment (i.e., chronic aphasia); 220 patients will be screened for participation, with the goal of including at least 126 patients during the 26-month recruitment period. Basic language production and comprehension abilities need to be preserved (as assessed by the Aachen Aphasia Test).

Therapy consists of language-systematic and communicative-pragmatic exercises for at least 2 hours/day and at least 10 hours/week, plus at least 1 hour self-administered training per day, for at least three weeks. Contents of therapy are adapted to patients’ individual impairment profiles.

Prior to and immediately following the therapy/waiting period, patients’ individual language abilities are assessed via primary and secondary outcome measures. The primary (blinded) outcome measure is the A-scale (informational content, or 'understandability’, of the message) of the Amsterdam-Nijmegen Everyday Language Test (ANELT), a standardized measure of functional communication ability. Secondary (unblinded) outcome measures are language-systematic and communicative-pragmatic language screenings and questionnaires assessing life quality as viewed by the patient as well as a relative.

The primary analysis tests for differences between the therapy group and an untreated (waiting list) control group with respect to pre- versus post 3-week-therapy (or waiting period, respectively) scores on the ANELT A-scale. Statistical between-group comparisons of primary and secondary outcome measures will be conducted in intention-to-treat analyses.

Long-term stability of treatment effects will be assessed six months post intensive SLT (primary and secondary endpoints).

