#### *Primary analysis*

The primary endpoint will be evaluated at baseline (t1) and immediately after 3 weeks of intensive therapy/waiting period (t2), by a statistical between-group comparison of the ANELT A-scale (ANCOVA) in an ITT design and with methods of multiple imputation taken into account. We expect that monotone missing data patterns will be observed (as described in [33]) and techniques appropriate for this situation will be applied. As a sensitivity analysis, the last-observation-carried-forward method will be applied.

Based on prior studies, we expect a therapy-induced improvement on the ANELT A-scale of M = 10 points (SD = 14) from baseline to immediately after 3 weeks of intensive therapy in the intensively treated group. For the waiting list group, we expect a change of M = 1 point (SD = 10) from baseline (t1) to the end of the 3-week waiting period (t2).

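### The stated difference (10 points), power (90%) and 63 per group do not agree with the plan's own inputs: the difference is 9 points and power about 98% under normality

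*Protocol article*

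**What the plan says.** All references are to the protocol article. The Power calculation section states that "group sample sizes of 63 were specified for each group in order to achieve 90% power to detect a difference of 10 points" in mean improvement between the groups. It gives the comparator as "the waiting list group (difference of 1 point after 3 weeks of waiting"), and the variability as "assuming a standard deviation for the difference in the ANELT A-scale score between t2 and t1 of 14 (10 for the waiting list group"). On the test it says: "Sample size was calculated for a two-sided Mann-Whitney test with significance level (alpha) of *P* <0.05". It adds: "The assumption of non-parametrical testing is rather conservative and the actual power will be larger if parametrical testing is possible".

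The Primary analysis section repeats the planning values. For the therapy group, "we expect a therapy-induced improvement on the ANELT A-scale of M = 10 points (SD = 14"). For the comparator: "For the waiting list group, we expect a change of M = 1 point (SD = 10) from baseline (t1") to the end of waiting.

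The Power calculation section also names 8 points as the smallest clinically significant difference. It allows 25% non-participation before randomisation, which raises 63 to 84 per group. The Abstract gives the matching total, "with the goal of including at least 126 patients during the 26-month recruitment period".

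**The concern.** The section prints every input a reader needs to recompute the sample size, and the result does not follow from them. There are two mismatches. First, 10 points is called the between-group difference, although the waiting list is itself expected to gain 1 point. Second, 63 per group is more than 90% power requires at 9 or at 10 points with the stated SDs.

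This calculation sizes the only confirmatory test in the trial. A reader who takes the sentence at face value will conclude that power is 90% at 10 points, and so lower at the 8-point clinical threshold. On the stated inputs, power at 8 points is itself above 90% under normality. If instead 63 came from other inputs, the printed assumptions are not the ones used. In both cases the article misreports what the trial was built to detect.

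**Working it through.** **Inputs.** Two-sided alpha 0.05, Mann-Whitney test, 63 per group and SDs of change 14 and 10 (Power calculation). Mean changes 10 and 1 (Primary analysis; the 1 also in Power calculation).

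**Difference.** 10 − 1 = 9 points.

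**Does 63 at 90% reproduce?** Normal approximation per group:

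n = (1.960 + 1.282)² × (14² + 10²) / d² = 10.51 × 296 / d²

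For the Mann-Whitney test with normal data, divide by its relative efficiency, 3/π = 0.955.

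| d | n for 90%, normal approximation | n for 90%, Mann-Whitney |
|---|---|---|
| 10 | 31.1 | 32.6 |
| 9 | 38.4 | 40.2 |
| 8 | 48.6 | 50.9 |
| 7 | 63.5 | 66.5 |

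Neither 10, 9 nor 8 points gives 63. Only 7 points without a rank-test penalty comes close.

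**Power with 63 per group.** The standard error of the difference is √(296/63) = 2.168. Power = Φ(d√0.955 / 2.168 − 1.960).

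| d | Mann-Whitney, formula | Mann-Whitney, simulated with normal data |
|---|---|---|
| 10 | 99.5% | 99.3% |
| 9 | 98.2% | 98.0% |
| 8 | 95.0% | 94.5% |
| 7 | 88.4% | 88% |

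**Difference with 90% power at 63 per group.** 3.242 × 2.168 = 7.03 points by normal approximation; 7.03 / √0.955 = 7.19 for the Mann-Whitney test. Simulated power at 7.2 points is just under 89%, so the exact value is slightly higher.

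**Does the choice of a rank test explain 63?** With the lowest efficiency usually quoted, 0.864, n at 9 points is 38.4 / 0.864 = 44.4 and power at 63 is 97.1%. That bound applies to a pure shift between distributions of the same shape, and the SDs here differ, so it is not a true worst case. Simulation is more informative. Keeping the stated means and SDs but giving the therapy-group change a right-skewed gamma shape (skewness 1 to 2, normal controls), power at 63 is about 95–96%. At 42 per group, power is about 90% with normal data but only about 84–85% with that skewness.

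**Does the 25% allowance explain 63?** No. 63 / 0.75 = 84, so the allowance is added on top of 63, and it applies before randomisation.

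**The case against.** The strongest reply is that 63 has a plausible origin in the section itself. The sentence opens with the 8-point clinical minimum; 8 less the 1-point waiting-list change is 7. With the stated SDs and alpha, the normal approximation for 7 points gives 63.5 per group, and 63 give 89.8% power. On that reading N is sound and only the reported target is wrong. This stands as a possibility, but it is inference: the article does not describe it, and it leaves out the penalty for the Mann-Whitney test that the article says was used (simulated power at 7 points is 88%). Other departures from the printed inputs also come near 63; for example, 8 points with SD 14 in both groups gives 65.

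It is also fair to say that 98% rests on normal data, while the section presents the rank test as the cautious choice. With moderate skewness the figure is 95–96%, still above 90%. A sufficiently extreme shape can reverse this: a mixture in which 30% of treated patients respond gave 83%. The article states no such distribution.

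Two stronger readings are tempting and not supported. A reader might infer that the trial is underpowered; on the stated inputs the discrepancy runs the other way. A reader might also infer that the trial is about 20 per group too large because 42 would do; that holds only under normality.

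Finally, the consequences are limited. The 9 points can be recovered from the Primary analysis section, a null result would be judged mainly by its confidence interval, and missing outcomes are addressed by multiple imputation with a last-observation-carried-forward sensitivity analysis. Imputation does not restore lost information, but loss after randomisation is not ignored.

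**Conclusion.** The point holds as an inconsistency in the reported sample-size calculation. The planning means give a difference of 9 points, not 10. For 9 points, 63 per group have about 98% power under normality and about 95–96% with a moderately right-skewed therapy-group change; the stated 90% understates it. Under normality, 90% power corresponds to about 7.2 points, which lies below the 8-point clinical threshold. These figures take the printed SDs, alpha and test as given, with all 63 per group evaluable. How 63 was obtained cannot be settled from the article. The test, the alpha, the analysis and the enrolment target are unaffected.

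**What to change.** Keep 63 per group and rewrite the Power calculation paragraph:

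- Give the between-group difference in mean change as 9 points (10 versus 1; SDs 14 and 10).
- State that 63 evaluable patients per group give about 98% power for 9 points with a two-sided Mann-Whitney test at 0.05 under normality, and 90% power for about 7.2 points. A note that moderate skewness lowers the first figure to about 95–96% would help.
- State what produced 63: a 7-point target (8 less 1), other SDs, or an allowance for loss after randomisation. If it was an allowance, give its size.
- Do not write that about 42 per group would suffice unless the normality condition is stated with it.

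The cost is one paragraph. Recruitment, randomisation and analysis do not change.

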### Statistical analyses

Analyses of primary and secondary endpoints will be performed in the (intention-to-treat) ITT population consisting of all randomized patients who received at least one day of therapy, or were at least one day on the waiting list. If data are normally distributed, parametrical methods will be used. The primary analysis will test for differences between the therapy group and the untreated (waiting list) control group with respect to the mean change (relative to baseline performance at the test point prior to the instantiation of therapy) on the ANELT A-scale at the test point immediately following the 3-week intensive therapy (or respective waiting) period. As opposed to the comparison group, which is not expected to demonstrate a clinically significant change between the two baseline assessments prior to SLT on the ANELT A-scale scores, the therapy group on average is expected to show a clinically significant improvement between the two test points. In the following paragraphs, statistical analyses are explained in more detail.

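### The population called ITT admits therapy-arm patients only once therapy has begun but waiting-list patients after one day of waiting, so the confirmatory comparison is a one-day modified ITT

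*Protocol article*

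**What the plan says.** The Statistical analyses section assigns the primary and secondary endpoints to an ITT population made up of "all randomized patients who received at least one day of therapy, or were at least one day on the waiting list". The Primary analysis section then compares the arms from t1 to t2 "by a statistical between-group comparison of the ANELT A-scale (ANCOVA) in an ITT design and with methods of multiple imputation taken into account", with last observation carried forward as a sensitivity analysis. The abstract also describes the between-group comparisons as intention-to-treat.

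The Procedure section gives the timing: "Depending on their group assignment, patients either start therapy immediately (experimental group) or 3 weeks after the initial baseline session". The primary endpoint at t2 therefore falls before any waiting-list patient has begun therapy.

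Secondary analyses adds a per-protocol version of the t1–t2 comparison. The end of the Waiting list control group section says that only the primary analysis of the primary endpoint counts as strictly confirmatory.

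**The concern.** Intention-to-treat protects the comparison because membership is settled at randomisation. Here membership depends on something that happens afterwards, and the hurdle differs by arm. To be counted, a therapy-arm patient must begin treatment. A waiting-list patient only has to remain on the list for a day, and is counted even if therapy never follows. Patients of the same kind can thus be dropped from one arm and kept in the other.

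A common defence of a modified ITT set is that exclusion cannot depend on allocation. It is not available here, because the design is open (PROBE) and the criterion itself is specific to the arm.

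At stake is whether the trial's single confirmatory estimate is the effect of assigning patients to intensive therapy, or a contrast between therapy starters and nearly all waiting-list patients.

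**Working it through.** **The rule applied to each arm**

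- Assigned to therapy, never starts: no day of therapy and no day on the waiting list. Excluded.
- Assigned to therapy, stops after one day: included.
- Assigned to waiting, withdraws the same day: excluded.
- Assigned to waiting, waits one day or more, never starts therapy later: included.

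Multiple imputation and last observation carried forward act on missing values within the set, so they do not bring excluded patients back. The per-protocol analysis does not either.

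**Inputs**

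- Expected change t1 to t2: 10 points (SD 14) with therapy and 1 point (SD 10) with waiting (Primary analysis).
- 63 patients per arm, and 8 points as the minimum clinically significant difference (Power calculation).
- f, the share of the therapy arm that never starts: not in the document, so a range of 2% to 10% is assumed.
- Non-starters' change: not in the document. It is assumed equal to the expected waiting-list change of 1 point.

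**The plan's own difference.** Taking 10 as the change among patients who start, the stated set gives 10 − 1 = 9 points, whatever f is.

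**All randomised patients.** Difference = (1 − f) × 10 + f × 1 − 1 = 9(1 − f). Overstatement = 9 − 9(1 − f) = 9f.

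| f | Patients out of 63 | All-randomised difference | Stated set | Overstatement |
|---|---|---|---|---|
| 2% | 1.3 | 8.82 | 9 | 0.18 |
| 5% | 3.2 | 8.55 | 9 | 0.45 |
| 10% | 6.3 | 8.10 | 9 | 0.90 |

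The all-randomised difference reaches the 8-point threshold when 9(1 − f) = 8, so f = 1/9 = 11.1%, or 7 of 63. It is lower beyond that.

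**Power.** The root-mean-square SD is √((14² + 10²)/2) = 12.17. With 63 per arm, power by normal approximation is 0.986 for 9 points and 0.962 for 8.10 points. Under the worst-case Mann-Whitney efficiency of 0.864, the figures are 0.971 and 0.935. Loss of power is not the issue.

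**If therapy has no effect.** Suppose non-starters would change g points less than the rest. They are missing from the therapy arm and present among controls, so bias = f × g. The standard error is √(14²/(63(1 − f)) + 10²/63).

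- f = 10%, g = 5: bias 0.5 points, standard error 2.25, two-sided error about 0.056.
- f = 20%, g = 10: bias 2.0 points, standard error 2.34, two-sided error about 0.137.

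If non-starters would do better than the rest, g is negative and the bias runs against therapy. The document gives neither f nor g, so these are illustrations only.

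**What imputation would do.** If non-starters are brought back and their t2 is imputed from treated patients in the same arm (change about 10), the difference is (1 − f) × 10 + f × 10 − 1 = 9. The overstatement returns in full.

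**The case against.** The strongest reply is that non-starters will be few. The Power calculation section lists "no therapy funding by the respective sickness fund" among the reasons for non-participation before randomisation. Those patients are never randomised and cannot be dropped from one arm. According to Secondary analyses, it is the extension of funding that is decided after therapy has begun, when the one-day condition is already met. The therapy arm is also meant to start at once, which leaves a short window. All of this stands. A reader might infer that loss of funding empties the therapy arm selectively, but the document does not support that. Illness, withdrawal and non-arrival after randomisation remain possible, at a rate the document does not state.

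A second reply is that the direction is not established. This also stands in part. A reader might infer that the rule necessarily favours therapy. That follows if therapy works as the plan expects and non-starters change like controls. Under no effect, it depends on a prognosis that is not given.

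A third reply is that the conclusion is unlikely to change. At up to 10% non-starters the all-randomised difference stays at 8.10 or more, above the 8-point threshold, and power stays high. That is fair as to size. A larger overstatement could be obtained by assuming that non-starters get worse, but the plan expects untreated patients to gain 1 point over three weeks, so nothing in it supports such a decline.

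None of these replies removes the defect, which is an arm-specific entry rule in the only confirmatory analysis.

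**Conclusion.** The point holds. The stated set is a one-day modified ITT with an entry rule that differs by arm. The sole confirmatory test uses it, and the article describes no analysis of all randomised patients. This is a rule the article fixes, not a detail left to a statistical analysis plan.

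The likely size is modest: about 0.2 to 0.9 points on an expected 9, for an assumed 2% to 10% of non-starters who change like waiting-list patients. Both assumptions are outside the document.

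Two descriptions would go too far. The rule does not keep every waiting-list patient, since a same-day withdrawal is lost. Nor is the set defined by treatment received in the usual sense: a patient who stops after one day of therapy stays in, and nobody is moved between arms.

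**What to change.** Define the primary ITT set as all randomised patients, analysed in the arm assigned, whether or not therapy or waiting began. Attempt the t2 assessment in therapy-arm patients who never start. Where t2 is missing for them, impute it without treating them as treated, for example from waiting-list patients, and state that assumption. Adding them to the planned multiple imputation without this step would not be enough. Keep the present set as a supplementary analysis, labelled modified ITT.

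The cost is a short change to the analysis text, t2 attempts in what may be a few patients, one stated imputation assumption and a possibly slightly smaller estimate.
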